#### Respiratory and allergy

Forced expired volume in one second (FEV_1_) and forced vital capacity (FVC), before and 15 minutes after salbutamol (200 mcg) delivered via a metered-dose inhaler and spacer, are measured using an Easyone^TM^ spirometer and compared with predicted values [51]. Participants are asked to withhold short-acting inhaled bronchodilators for at least eight hours prior to spirometry and long-acting bronchodilators for 48 hours where possible. Spirometry is rescheduled if the participant has undergone eye surgery or has had a detached retina, heart problems or abdominal or chest surgery in the last 3 months, or has had influenza or a chest infection within the last 2 weeks. Swabs of the posterior wall of the oropharynx are collected and stored for later bacterial identification by DNA sequencing. DNA will be extracted from the swabs and submitted to PCR amplification of the V3-V5 variable region of bacterial 16S rRNA. Skin prick tests to common aero-allergens (Grass Mix #7, Rye Grass Pollen, dust mites: *Dermatophagoides pteronyssinus* and *Dermatophagoides farinae*, Cat-Pelt, Dog Hair Dander, Mould Mix #10, *Alternaria tenius* and *Aspergillus fumigatus* (Stallergenes, France)) is performed on the anterior forearm. Wheals 3 mm, or greater, in diameter measured at 15 minutes post-application and pricking are scored as positive reactions. Negative (glycerine) and positive (histamine) controls are used. Participants are asked to refrain from taking antihistamine medications for at least 1 week prior to allergy testing, where possible.

#### Ears and hearing

Otoscopic examination of the external auditory canal is performed using a Mini 3000 otoscope (Heine, Germany) and visibility of the tympanic membrane, outer ear structures, obstructions and discharges are noted. Ear canal volume, middle ear pressure and compliance of the tympanic membrane are measured using an Otowave tympanometer (Amplivox Ltd, United Kingdom). Tympanometry is rescheduled if a participant has undergone ear surgery, perilymph fistula or barotrauma within the previous three months. Pure tone air and bone conduction thresholds are determined using automated audiometry with AMTAS software (AMTAS, Audiometry Incorporated, USA) controlling a Conera audiometer (GNOtometrics, Copenhagen, Denmark), with Sennheiser HDA 200 (Wennesbostel, Germany) headphones, on a NOAH platform (Hearing Instrument Manufacturers’ Software Association, Copenhagen, Denmark) and conducted in a sound-proof booth (Acoustic Designs, Australia) [52]. The participants are first instructed through the headphones. The testing protocol is in accordance with Hughson-Westlake methods. Participants are asked to respond with “Yes” or “No” after the presentation of every stimulus using a touch screen. Air conduction thresholds are recorded at 250, 500, 1000, 2000, 4000 and 8000 Hz, and bone conduction thresholds at 500, 1000, 2000, and 4000 Hz.

#### Eyes and vision

Intraocular pressure (IOP) is measured using a rebound tonometer (Icare, USA) and the average of 6 measurements for each eye is recorded in millimetres of mercury (mmHg). Keratometric and autorefraction measurements are taken using a handheld Auto Ref/Keratometer ARK-30 (Nidek, Japan) to assess refractive errors and to determine corneal curvature radius (corneal refractive power). A high-resolution digital retinal camera (Canon CR-1, Japan) is used to capture two images, one centred on the optic disc and the other centred on the macula. These images are assessed for pathological features of age-related macular degeneration and glaucoma. All eye assessments are conducted after dilation of the pupil using a mydriatic solution (tropacamide 1%) administered 15 to 20 minutes prior to testing.

#### Physical function, neuromuscular strength and power

Dynamic muscle power and strength of the leg extensors are assessed using a Ballistic Measurement System (Fitness Technology, Australia) which incorporates a force plate (400 series, Fitness Technology, Australia) for measurement of ground reaction force [53]. Participants are asked to perform a countermovement vertical jump for maximum height from the force plate and the highest power output and force reproducible to within 5% from up to 8 trials is recorded. A number of parameters are measured or derived including peak and average force, impulse, peak and average power output, peak velocity, maximum rate of force development, and jump height. Participants with current back, hip, knee or ankle pain may withdraw from the jump test at their discretion. Mobility is measured using the timed up and go (TUG) test [54]. Lower-body muscle power and balance is also assessed using the Five Times Sit to Stand Test (5TSTS) [55]. The test involves recording the time taken for the participant to perform 5 successive chair rises from a seated position with arms folded across the chest. Hand grip-strength is measured in kilograms using a hand dynamometer (Model 78010, Lafayette Instrument, USA) with the results of 3 trials (within 5%) recorded for each hand.

#### Balance and risk of falling

Static balance is assessed using a force plate (400 Series, Fitness Technology, Australia) with vertical forces analysed to determine the centre of pressure on the plate. A modified clinical test of sensory interaction on balance involves the participant standing stationary for 30 seconds on the force plate during four conditions; a) eyes open and b) eyes closed, while standing on a stable surface, *and* c) eyes open and d) eyes closed, while standing on an unstable surface [56]. During these trials movement of the centre of pressure and postural sway is recorded using Inner Balance software (Innervations, Australia).

#### Cognition

Cognitive testing focuses on episodic memory assessment, as well as tests of attention and executive function. Memory and attention is assessed using the Cognitive Drug Research (CDR) [57] computerised assessment system (United BioSource Corporation, UK). This has been used extensively in clinical and longitudinal studies, including the dementias, over the last 20 years, has been shown to be sensitive to subtle cognitive changes, and has the largest normative database of its kind [57]. The battery consists of several key tasks including: immediate and delayed word recall and recognition, simple and choice reaction time, digit vigilance, spatial and numeric working memory and delayed picture recognition. Participants also complete measures of retrieval ability and executive functioning using the phonemic (letters C, F, L) and semantic (category - animal) fluency test with trials conducted over 1 minute [58]*.* Pre-morbid intelligence is estimated from scores on the Australian National Adult Reading Test (AusNART) [59] and used as an index of cognitive reserve. Participants also complete the Mini Mental State Examination (MMSE) [60].

#### Sleep-disordered breathing

Sleep apnoea screening devices are offered to participants to use over one night at home. Sleep studies are undertaken using dual channel (oximetry & nasal pressure) ApneaLink™ devices (Resmed, Australia). Participants are instructed on how to fit and operate the units and are also provided with an instruction card and tape for cannula attachment to the cheek. The monitors are returned to the study centre the following day. Data are downloaded and automatically analysed using ApneaLink software version 8.00. Scores of respiratory disturbances including snoring events, apnoea hypopnea index and oxygen desaturation and duration are recorded. Each participant is provided with a score sheet and explanatory guide to indicate the level of sleep–disordered breathing based upon risk index scores at different cut-offs (normal <5, mild 6–20, moderate 21–30 and severe >30). Participants who receive current CPAP or mandibular advancement splint therapy for sleep apnoea are excluded from the sleep apnoea screening study.

### Information provided to participants

Following completion of the testing protocol and return of the questionnaire, participants receive an explanatory guide and copy of the following test results: height, weight, waist measurement, haematology and biochemistry, lung function, skin test responses, cardiovascular profile (blood pressure and ankle-brachial index), bone density, audiometry and sleep apnoea screening test. All results from the physical tests are discussed with the senior scientist onsite and blood tests are posted to participants after being reviewed by the study chief clinical investigator. Participants are urged to provide a copy of their results to their general practitioner where indicated.

### Data capture and management

Hard copies of questionnaires are converted to electronic portable document file (PDF) format and data are extracted and verified on-site using Cardiff TELEform software (Verity Inc. Sunnyvale, CA). These data, along with automatic data capture capabilities from most of the devices being used are stored with the existing Busselton Health Study collection which is managed by the School of Population Health, University of Western Australia.

### Quality control

Each study participant is taken through the testing protocol by a single research assistant. Therefore, all research assistants are trained in all aspects of testing. Training is conducted on-site and, where necessary, within the laboratories of each of the participating investigators under the supervision of experienced laboratory staff, until the required standard of testing and competency is achieved. Raw data are reviewed weekly in-house or within the laboratories of investigators to ensure that standards are maintained, with regular feedback to research assistants and further instruction or adjustments provided where necessary. Complex interpretation and review of results from retinal photographs and bone density scans are undertaken off-site by experienced, specialised staff within the participating laboratories. All equipment is maintained, serviced and calibrated according to manufacturer’s specifications and schedules.

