### Aims

The general aim of the BHAS is to identify the cumulative effects of disparate illnesses that constitute the burden of disease that impacts on healthy ageing, starting with a detailed assessment of physical function, cognitive performance and quality of life in baby boomers’.

The specific aims of Phase 1 of the study are to:

1. Determine:

a) Prevalence of chronic physical and mental illness

a) Prevalence of potential multiple-domain risk factors

a) Quality of life and health burden, in 4000 baby boomers from a community-dwelling population sample.

2. Determine the clustering within individuals of:

a) physical and mental illnesses

a) potential risk factors.

3. Determine clustering, across individuals, of:

a) physical and mental illnesses

a) risk factors

a) burden of illness, based on age, sex, and socio-economic factors.

4. Examine associations between illness clusters and risk factor clusters.

5. Collect and store serum, DNA and RNA from blood samples for future studies of genetic risk factors and gene-environment interactions and for the identification of biomarkers associated with ageing and disease.

6. Provide a baseline for follow-up assessments to enable analysis of changes in risk factors and outcomes with a view to determination of factors that impact on healthy ageing, healthcare utilization, employment and occupation, residential setting, and community participation.

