### Questionnaire data collection

All participants who attend the testing centre complete a self-administered questionnaire that collects information on the following:

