#### Blood sample

A fasting venous blood sample is collected from the cubital fossa in evacuated clot, fluoride/oxalate, ethylenediaminetetraacetic acid (EDTA) and gel serum separator tubes (SST) (BD Biosciences, Australia). Whole blood is also collected in PAXgene® blood tubes for preservation of RNA for later gene expression studies. A range of haematological and biochemistry tests (Table 2) is conducted on fresh samples by PathWest laboratories (Busselton and QEII Medical Centre, Nedlands, Western Australia). Serum, plasma and buffy coat fractions are processed and separated onsite for biospecimen banking. DNA and RNA will be extracted and stored by the Western Australian DNA Bank.

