#### Determination of the aggregation, clustering and distribution of illnesses (burden of illness)

Burden of illness will be based on the number and specific types and combinations of illnesses. Frequency (contingency) tables and logistic regression methods will be used to investigate relationships between illnesses and how these vary across socio-demographic groups. Generalised linear regression methods will be used to identify risk factors for number and combinations of illnesses (and symptoms) and compare these with the standard risk factors for individual illnesses. Cluster analysis methods (e.g. k-means cluster and latent class analysis) will be used to identify clusters of people who are homogeneous with respect to risk factors and symptoms and then contingency table methods will be used to explore the relationships between the clusters and specific illnesses and combinations of illnesses.

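### One research assistant tests each participant throughout, so examiner error is shared across that person's assistant-administered tests and can produce spurious associations between them

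*Protocol article*

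**What the plan says.** The Quality control section fixes the allocation of testers: "Each study participant is taken through the testing protocol by a single research assistant". It draws the consequence for training: "Therefore, all research assistants are trained in all aspects of testing". It gives two further safeguards that bear on examiner differences. One is ongoing: "Raw data are reviewed weekly in-house or within the laboratories of investigators to ensure that standards are maintained", with feedback to staff. The other takes some readings away from the assistant: "Complex interpretation and review of results from retinal photographs and bone density scans are undertaken off-site by experienced, specialised staff".

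Specific aim 2 begins "Determine the clustering within individuals of" and covers both illnesses and risk factors. Aims 3 and 4 extend this to clustering across individuals and to associations between illness clusters and risk factor clusters. In the section on aggregation and clustering, k-means and latent class methods "will be used to identify clusters of people who are homogeneous with respect to risk factors and symptoms". The section on function and quality of life regresses cognitive and physical function and SF-12 on illnesses, symptoms and risk factors.

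Two large blocks of data do not pass through the assistant's hands or judgement. For the questionnaire: "All participants who attend the testing centre complete a self-administered questionnaire that collects information on the following". For haematology and biochemistry, testing "is conducted on fresh samples by PathWest laboratories".

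**The concern.** Examiner variation in a single measure mostly adds noise. For an association between two measures it matters more when the same examiner took both, because the examiner is then a common source of error in the two. An assistant who reads girths high and coaches spirometry hard gives both features to the same set of people. Under this allocation, that sharing cannot be told apart from true association within the person unless the assistant is identified in the data. Training and weekly review can shrink the examiner component, but they cannot separate what remains.

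The exposed measures are those in which the assistant's technique, judgement or encouragement can matter: neck, waist and hip girth, Mallampati and pharyngeal grade, spirometry effort, wheal diameter, grip, jump, timed up and go, chair rises, fluency, AusNART and MMSE. Several are outcomes in the function models. Girths, lung function and skin test responses can enter the same models as risk factors, or can be inputs to the cluster analysis. The Limitations section names relationship estimates, rather than prevalence, as the main interest of the study, and this is where a shared examiner has its effect.

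**Working it through.** **The plan's own figures.** The article gives no figure for examiner variation. Its precision statement reproduces: 4,000/38 = 105 per sex and birth-year group, with standard errors √(0.10 × 0.90/105) = 0.029 and √(0.25 × 0.75/105) = 0.042. Its claim of over 85% power also reproduces: at two-sided 5% (assumed), the lowest value is 86.4%, for 0.25 against 0.30 with 1,000 against 3,000 people. Neither figure bears on this point.

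**Inputs.** n = 4,000, from the Data analysis and statistical power section. Assumed, because the article does not give them: J = 6 or 10 assistants with equal workloads, and an examiner share of variance v of 1%, 3% or 5% in each measure. The two measures are truly unrelated.

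**Case A: an assistant's effects on the two measures are unrelated.** The spurious correlation has mean zero and standard deviation v√(J−1)/J. Sampling error adds 1/√4,000 = 0.0158. The total standard deviation is the root of the sum of squares. The nominal 5% test then rejects with probability 2Φ(−c), where c = 1.96 × 0.0158/total.

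| J | v | SD from examiner | Total SD | c | Rejection, formula | Rejection, simulation |
|---|---|---|---|---|---|---|
| 6 | 1% | 0.0037 | 0.0162 | 1.91 | 5.6% | 5.4% |
| 6 | 3% | 0.0112 | 0.0194 | 1.60 | 11.0% | 11.8% |
| 6 | 5% | 0.0186 | 0.0244 | 1.27 | 20.5% | 18.9% |
| 10 | 1% | 0.0030 | 0.0161 | 1.93 | 5.4% | 5.1% |
| 10 | 3% | 0.0090 | 0.0182 | 1.70 | 8.8% | 8.7% |
| 10 | 5% | 0.0150 | 0.0218 | 1.42 | 15.5% | 14.9% |

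The simulation used 3,000 datasets per row. A separate run with 6 assistants gave 11% at 3% and 21% at 5%. The ranges are therefore about 5 to 6% at a 1% share, 9 to 12% at 3%, and 15 to 21% at 5%.

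**Case B: an assistant's effects tend the same way on both measures.** If those effects correlate at ρ, the expected spurious correlation is about vρ. With v = 5% and ρ = 0.5 this is 0.025; the simulated means were 0.020 and 0.022, and rejection was 33% and 35% (6 and 10 assistants). With v = 2% and ρ = 0.5, rejection was 12% and 10%, with a mean correlation of just under 0.01.

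**Checks that isolate the cause.**
- With separate examiners for the two tests, rejection stays at about 5 to 6%.
- With only one of the two measures examiner-dependent, it is 4.9%.
- With the assistant means removed, it returns to 4.2 to 5.6% in Case A, and to about 4 to 7% across the wider set of scenarios.

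The inflation therefore needs the same examiner and two examiner-dependent measures, and adjustment for assistant removes it.

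**Clustering.** A simulated k-means analysis of such measures gave cluster membership that depended on the assistant. The degree was not quantified, so only the direction is claimed.

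**The case against.** The strongest objection is scope. A reader might infer from the single-assistant rule that all of a person's measures share examiner error, and that the illness clustering sought in aim 2 could be an artefact. The documents do not support that. Diagnoses, symptoms, mental health, lifestyle and SF-12 come from the self-administered questionnaire. Bloods go to a laboratory, audiometry is automated, the home sleep study is scored by software, and retinal and bone images are interpreted off-site. If one side of an association is free of the examiner, and assistants are unrelated to illness, the test keeps its level. Most illness and symptom clustering, and most models of function on illness, are in that position. This part of the objection stands.

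Second, the effect is small, and its size is assumed. A correlation of 0.02 reaches significance only because n is 4,000, and nobody would read it as important clustering. Competency training, weekly review, the 5% reproducibility rule for jump and grip, and the controls for skin tests all exist to keep examiner variance low. At a 1% share there is almost nothing to correct. This stands too, and it limits how seriously the point should be taken.

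Third, a condensed article need not list covariates, staff codes or rosters, and nothing in it says that the assistant's identity goes unrecorded. That is correct: the absence of an examiner term is not in itself an error. The point rests instead on the stated allocation rule, set against aims that depend on association across measures. A later analysis plan can deal with it only if the identity was recorded.

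A reader might also suspect that staff turnover aligns examiners with calendar time. The article does not describe turnover, and invitation order is randomised, so nothing is built on that.

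**Conclusion.** The point holds for pairs of assistant-administered tests and for cluster analyses that use them. There the allocation rule makes the examiner a shared source of error that the stated quality control can reduce but not separate. It does not hold for the study's data as a whole.

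With 6 to 10 assistants, the excess over a nominal 5% is negligible at an examiner share of about 1% and material from about 3 to 5%. The spurious correlations have a standard deviation of about 0.02 at the 5% share, or a mean of about 0.02 if an assistant's tendencies also correlate at 0.5. The number of assistants, the variance shares and the alignment of tendencies are all assumptions.

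The practical risk is a scatter of weak but significant cross-domain findings among physical, respiratory, allergy and cognitive tests. The design is workable and the problem can be corrected in analysis, provided that the assistant can be identified for each visit. That makes this a recommended change and not a fatal flaw.

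**What to change.** 1. Record the assistant's code at every visit, or confirm that it is already recorded. This cannot be recovered later.
2. Allocate assistants to appointments by rotation, without regard to participant characteristics.
3. Include assistant as a fixed effect in models where both outcome and predictor are assistant-administered.
4. Before k-means or latent class analysis, centre the assistant-administered inputs on the assistant's mean. Then tabulate cluster membership by assistant.
5. Report the examiner share of variance for these tests, which would replace the assumptions above with data.

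The cost is one field per visit and, with 6 to 10 assistants, 5 to 9 degrees of freedom in a model on about 4,000 people. No test, procedure or staffing has to change.

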### Data analysis and statistical power

It is expected that most analyses will be based on adequate data for about 4,000 people (with about equal numbers of men and women and with relatively uniform numbers across the year-of-birth groups). The statistical approaches used to investigate the aims of the BHAS Phase 1 are:

#### Estimation of the prevalence of multiple chronic disease processes

Questionnaire results and the results of physical and cognitive testing will be recorded to calculate the prevalence of diagnosed illness, medication use, current symptoms, current cognitive and physical functional status, quality of life and risk factors for disease. Logistic regression and linear regression methods will be used to compare and analyse trends in prevalence and mean levels and to investigate risk factors for illnesses. With 4,000 participants, there will be an average of 105 people in each sex-year-of-birth group and this will allow the prevalence (as a proportion) in each group to be estimated with standard error of 0.03 to 0.04 (for prevalence proportions ranging from 0.1 to 0.25) and much more accurately when groups are aggregated or estimates are based on fitted logistic models. This sample size will provide over 85% power to detect differences as small as 0.05 in prevalence proportions (ranging from 0.1 to 0.25) between men and women or between groups defined by risk factors and symptoms with prevalence around 25%.

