## Methods/design

### Study sample and recruitment process

The Busselton Shire comprises about 1.25% of the Western Australian population (25,355 people according to the 2006 Australian Census) and a total of 6,690 adults born from 1946 to 1964 are registered on the 2010 electoral roll in the region, with 48.4% being male and an average of 352 individuals per year of birth group. All non-institutionalised baby boomers who currently live in the Shire and listed on the electoral roll are eligible to participate. Order of invitation to participate is randomized, with recruitment efforts focused upon sequential 10% sample draws. Contact with participants is via a letter of introduction, followed by a phone call to invite them to attend the testing centre for a four hour appointment. Addresses are obtained from the electoral roll and phone numbers are obtained from local residential and business directories.

Phase I of the BHAS commenced mid-2010 and will run until 2013. Based on current recruitment progress and participation rates, it is anticipated that approximately 4,000 participants will be recruited and tested (59% of those listed on the electoral roll).

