#### Demographics

Age, sex, marital status, ancestry/ethnicity, highest education level obtained and age at completion, current and previous occupational history (including years spent in longest occupation and exposure to dust), household income, dwelling type, years lived at current dwelling and occupancy status.

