#### Lifestyle, activity and environment

Information on smoking history and exposure to environmental tobacco smoke at home or work is recorded along with alcohol consumption, dietary intake of meat, fruit, vegetable, dairy and cereals and also foods avoided or never eaten.

Physical activity and sedentary behaviour is assessed using the short form of the International Physical Activity Questionnaire*, IPAQ*[29]. The average number of hours of sleep obtained over a typical 24 hour period, exposure to occupational noise, and information on household floor coverings and pet ownership is also collected.

Information technology exposure including mobile phone, television, computer and internet usage is assessed using the Young People’s Activity Questionnaire [30]. Attitudes to information technology are assessed with the computer confidence subscale of the Computer Attitudes Scale [31] that has independently verified factor constructs [32].

Information on social inclusion and community values is collected using nine items from the Social Capital Questionnaire (SCQ) [33], which encompasses constructs of “*feelings of trust and safety*”, “*neighbourhood connections*” and “*proactivity in the social context*”. Information on life values, including self-reported importance of financial security, social and job status and personal relationships is also collected.

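### Cheap improvement: about 60% of one Shire's birth cohort is expected to enrol, so many participants will probably be co-resident partners, but the named Phase 1 methods make no allowance for household correlation

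*Protocol article*

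**What the plan says.** Under *Study sample and recruitment process*, the protocol article reports "a total of 6,690 adults born from 1946 to 1964 are registered on the 2010 electoral roll in the region". Eligibility is by individual: "All non-institutionalised baby boomers who currently live in the Shire and listed on the electoral roll are eligible to participate". Selection has no household stage: "Order of invitation to participate is randomized, with recruitment efforts focused upon sequential 10% sample draws". The expected yield is "approximately 4,000 participants will be recruited and tested (59% of those listed on the electoral roll". The same section says that addresses come from the electoral roll.

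The questionnaire covers several attributes that belong to a household rather than a person: "household income, dwelling type, years lived at current dwelling and occupancy status" under *Demographics*, and "information on household floor coverings and pet ownership is also collected" under *Lifestyle, activity and environment*.

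Under *Data analysis and statistical power*, "It is expected that most analyses will be based on adequate data for about 4,000 people". The prevalence section then claims a standard error of 0.03 to 0.04 per sex-by-birth-year group, and it says "This sample size will provide over 85% power to detect differences as small as 0.05 in prevalence proportions". That power claim is for proportions from 0.1 to 0.25, compared between men and women or between groups formed by a factor with prevalence around 25%.

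The three Phase 1 analysis subsections name logistic, linear and generalised linear regression, contingency tables and cluster analysis. Where clustering is mentioned, it means clustering of illnesses, symptoms or risk factors. Mixed models and GEE appear only under *Future longitudinal analyses*.

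**The concern.** If both partners in a couple were born in the eligible years, each can be invited, and nothing limits enrolment to one person per household. With about six in ten of the roll expected, co-enrolled couples are a likely product of the design. Partners tend to resemble each other in lifestyle and, to a lesser degree, in illness, and they share household attributes exactly.

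Positive correlation between partners makes independent-data standard errors too small for pooled prevalence and for associations with household-level exposures. It makes them too large for contrasts between the sexes. The article calls associations its primary focus and plans to examine burden of illness by socio-economic factors, some of which (household income, dwelling type) are household attributes. At stake is the accuracy of some confidence intervals. Point estimates are not in question.

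**Working it through.** **Inputs from the article.** N about 4,000; roll 6,690; 19 birth years × 2 sexes = 38 cells; difference 0.05; prevalence 0.10–0.25; groups of about 2,000 v 2,000 (sex) or 1,000 v 3,000 (a 25% factor).

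**Inputs assumed, because the article gives none.**
- Two-sided alpha of 5%.
- 70–80% of participants partnered, 70–90% of partners born 1946–1964, and 60–80% of those also attending.
- Within-couple illness correlation ρ of 0.1–0.3.
- Within-couple correlation of the exposure ρx of 1 if fully shared, and 0.2 as an example of an individual-level exposure.

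**Step 1: reproduce the article's figures under independence.**
- Sampling fraction: 4,000/6,690 = 59.8%.
- Cell size: 4,000/38 = 105. Cell SE = √(p(1−p)/105), which is 0.029 at p = 0.10 and 0.042 at p = 0.25. This matches 0.03–0.04.
- Power = Φ[(0.05 − 1.96·SE₀)/SE₁], with SE₀ from the pooled proportion and SE₁ from the two separate proportions. Example at 1,000 v 3,000, with 0.20 in the smaller group and 0.25 in the larger: SE₀ = 0.01554 and SE₁ = 0.01492, so power is 90.5%.

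| Contrast | 0.10 v 0.15 | 0.20 v 0.25 | 0.25 v 0.30 |
|---|---|---|---|
| Men v women, 2,000 each | 99.8% | 96.6% | 94.3% |
| 25% factor, 1,000 v 3,000 | 98.5–98.6% | 90.5–90.9% | 86.4–86.9% |

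The ranges show which group has the higher prevalence. The claim of over 85% is met in every cell.

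**Step 2: share of participants with an enrolled partner (f).**
Low: 0.70 × 0.70 × 0.60 = 0.29. High: 0.80 × 0.90 × 0.80 = 0.58.

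**Step 3: variance factors.**
- Overall prevalence, or a fully shared exposure: 1 + fρ. Low: 1 + 0.29 × 0.1 = 1.03. High: 1 + 0.58 × 0.3 = 1.17. The square roots are 1.015 and 1.08, so the SE is about 1.5–8% too small.
- Risk-factor contrast in general: 1 + fρρx. At ρx = 0.2 this runs from 1.006 to 1.035, a change in SE of 0.3–1.7%, or about 1%.
- Men v women, with opposite-sex partners: 1 − fρ, from 0.97 down to 0.83. The true SE is about 1.5–9% smaller than the independent one, and power rises.
- Sex-by-birth-year cells: opposite-sex partners fall in different cells, so the factor is 1.

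**Step 4: power for a 25% factor fully shared within households.** Both group sizes are divided by the design effect.

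| Design effect | 0.20 v 0.25 | 0.25 v 0.30 |
|---|---|---|
| 1.00 | 90.5–90.9% | 86.4–86.9% |
| 1.10 | 87.6–88.2% | 83.0–83.7% |
| 1.17 | 85.5–86.3% | 80.6–81.4% |

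With both proportions inside 0.10–0.25, power stays above 85% up to a design effect of about 1.18, just beyond the assumed ceiling. For 0.25 v 0.30 it reaches 85% at about 1.04–1.06.

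**The case against.** A reader might infer that the power figure is wrong and that Phase 1 standard errors are wrong throughout. The article does not support either inference.

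- **Power.** Read literally, both proportions lie in 0.10–0.25, and the figure then survives the whole assumed range of design effects, even for a fully shared exposure. For men versus women, the first contrast the sentence names, couple correlation raises power. It falls below 85% only for 0.25 v 0.30, which takes one proportion outside the stated range, combined with an exposure that partners share completely or nearly so. The sentence speaks of risk factors and symptoms, most of which are not household attributes.
- **Standard errors.** The direction depends on the contrast, and the cell standard errors do not move. For individual-level exposures the change is about 1%.
- **Silence.** The article never says that observations will be treated as independent. It names model families, and clustered variance can be used with those regressions. A condensed article commonly leaves the variance estimator to the full plan.
- **Magnitude.** The couple share and the correlations are all assumed.

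All four points stand, and they limit this to an improvement rather than an error. Two things remain on the other side. Co-enrolled partners are a likely consequence of the recruitment design. The article also names correlated-data methods for follow-up but none for Phase 1, so the matter is worth one sentence.

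**Conclusion.** The point holds as a low-cost improvement. No stated figure is contradicted, and the power claim need not be restated. A note that it assumes independent observations, and could be a few points lower for exposures fully shared within a household, is the most it needs.

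The mechanism follows from the recruitment design with good confidence. The size does not: the 1.5–8% understatement for overall prevalence and fully shared exposures rests on 29–58% of participants having an enrolled partner and on an illness correlation of 0.1–0.3, neither of which the article reports. Both can be estimated from the cohort itself once households are identified.

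**What to change.** Derive a household identifier from the electoral-roll address already held. Add one sentence to the three Phase 1 analysis subsections (prevalence; aggregation and burden of illness; function and quality of life) stating that regressions use household-clustered standard errors, either robust or from GEE. This handles both directions: intervals widen where partners' correlation inflates variance and narrow for contrasts between the sexes. Optionally, add to the power paragraph that it assumes independent observations.

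The cost is one derived variable and a variance option in the analysis code. Address matching will make some errors, for example when unrelated adults share an address or the roll is out of date. Intervals for pooled prevalence and household-level exposures become slightly wider. Recruitment and data collection do not change.
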